### Psychosocial aspects

Group singing is a leisure interpersonal activity with common goals, favoring empathy and social integration [15]. A few not controlled studies analyzed the impact of singing groups on psychosocial variables. Karp et al. (2006), in a longitudinal study, found that social activities have more impact when they involve a combination of psychosocial and physical components than when there is only one component, which is the case of group singing [19]. In the qualitative data of the Pires et al. (2017) study, social benefits were one of the most frequently reported advantages from participating in the singing group in the interviews, in terms of interpersonal interactions, levels of social support among seniors and sharing of positive emotions [13]. Stewart and Lonsdale (2016) compared choir singing with both solo singing and another leisure group activity (sports). They found that choir singers and team sport players reported higher levels of well-being than solo singers; moreover, the members of the choir experienced a stronger sense of being part of a meaningful group than the members of a sports group [8]. Thus, belonging to a group with an identity, to which individuals feel attached, may favor feelings of inclusion and social support. Participating in a choir, with vocal harmonizing and social interactions during rehearsals may favor interdependence and connection between the group members. Furthermore, increased social integration of the participants (higher perceived social support, lower feelings of loneliness, greater sense of social integration and identification with the group) may have positive consequences on their physical health [20–22].

The present study contributes with new results of the effects of singing on loneliness, identification with the social group, social well-being and quality of life (related with social relationships, with past, present, and future activities, and with social participation). The study will also test mediation effects of psychosocial variables of the effects of group singing program (such as group identification and loneliness) on the cognitive, mental and physical health variables of the participants.

### Cognitive functioning aspects

Group singing activity stimulates cognitive processes by focusing attention on the music, the teacher’s orientation, and the interaction with the other singers, memorizing lyrics, pitch and rhythm, factors which are known to stimulate executive, attention, verbal learning and memory functions [4]. Musical activities involve an extensive stimulation of the brain (nervous and neuroendocrine systems, temporal, frontal, parietal, cerebellar and limbic areas), capable of inducing long-term neuroplasticity and improving emotional and cognitive functions [23]. A few studies tested the impact of singing groups on the cognitive functioning of older adults with severe cognitive deficits. An RCT study by Särkämö (2014) with a dyadic intervention component, included people with dementia and their caregivers (*N* = 89), who acted as a coach, in two experimental conditions for a period of 10 weeks. Results showed that singing and listening to music were associated with improvements to remote episodic memory, attention, executive and general cognitive functions, while singing, specifically, revealed improvements in short-term and working memory. Benefits of the intervention, however, were more evident in individuals with early dementia [24]. Another study that compared singing activity and listening to music in older adults with dementia showed that singers reported significantly higher subjective well-being and cognitive ability improvements than listeners [25]. In another RCT study with older adults diagnosed with Alzheimers (*N* = 10), in which the music therapy group participated in weekly singing sessions for a period of 6 months, showed a significant decrease in the completion time of the Raven Matrix test and also in the results of the neuropsychiatric inventory between the pre and post-test intervention period of 6 months [26]. Functional magnetic resonance imaging revealed increased activity in the right angular gyrus and left lingual gyrus during participation in musical activity.

Fewer studies with singing groups included older adults with intact cognitive function or low cognitive deficits. Fu and collaborators (2018), in a quasi-experimental design, with 49 participants with no self-report of dementia, found that a singing group program of 75 min weekly sessions, for 12 weeks, with deep breathing training and song learning showed significant in promoting memory, language, speech information processing, and executive functions [10]. Clements-Cortes (2014) also included two small groups of 16 participants, one with intact cognitive function and another with dementia, in a chorus intervention for 10 to 16 sessions, yielding significant benefits in positive emotions and perceived pain, although, with no reports on cognitive benefits [27].

In sum, more RCTs are needed to test specific effects of choir singing on the cognitive functions of older adults with varying levels of cognitive function. Our study aims to contribute with causal effect results of a singing group program in terms of the general cognitive functions. We expect that weekly exercises of attention focusing on the lyrics, music and silent pauses, teachers’ instructions, and voices harmonizing with the group, and also with more social contacts and communication may work as a stimulation of the brain processes and structures. This stimulation can produce improvements in executive function, short-term memory, language, attention, working memory, verbal memory, and speed processing. The study also tests the hypothesis that cognitive function acts as a moderator of the effects of group singing on the physical and mental health of the participants.

### Health aspects

Aging is associated with declines in health, such as respiratory function, weaker lower limb strength and balance, cardiovascular disease, diabetes, high blood pressure, among others. In part, the individual’s physical decline is explained by a sedentary lifestyle and may be decelerated by keeping up physical activity and social participation. Participation in singing groups presupposes a regular physical and social activity, which requires changes to daily routines, increased physical activity, respiratory activity, mobility and longer periods standing up. Only a few experimental or quasi-experimental studies have provided evidence of measurable health benefits of a singing group activity [28]. In a quasi-experimental study, following participation in a choir program for 12 months and 24 months (Cohen et al. 2006, 2007), the intervention group reported a higher overall rating of physical health, fewer doctor’s visits, less medication use, fewer instances of falls, and fewer other health problems than the comparison group [29, 30]. However, due to methodologic and statistical analysis flaws of this study, analyzed in subsequent reviews of the literature [9, 31], these results should be considered very cautiously, and the hypotheses retested in future studies.

#### Physical activity and sedentary behavior

A recent study analyzing two large groups of older adults in the US and in the UK, using actigraphy to objectively measure these variables, found that about two thirds of awake time is devoted to sedentary activities, while only 2.5 up to 4.1% of subjects attained the 30 min/day moderate to vigorous physical activity recommendations [32].

#### Sleep quality

Sleep problems are increasingly common as one ages, and it is known that sleep duration is associated with all-cause mortality. There is an inverted U relationship between sleep duration and health problems, in that both short and long sleepers (< 6 h and > 8 h night, respectively) show a higher risk of developing health issues [33]. Both physical activity and sleep quality may be measured through actigraphy. However, none of these indicators have yet been analyzed as outcome measures of singing interventions in older adults.

#### Respiratory function

The aging process leads to a decline in the respiratory system resulting in changes to lung structure, the shape of the chest wall, thoracic muscles, and pulmonary vascular circulation [34]. Participating in group-singing activities, requires effort in breath management, including breathing support and control that may promote pulmonary health [10]. This result was found by Bonilha et al. (2009) in an RCT with 78 participants in a 6-month weekly singing program, improving lung function as regards inspiratory capacity, decreases in expiratory reserve volume and better maximal expiratory pressures, in patients with chronic obstructive pulmonary disease, following the singing therapy program [35]. The previously mentioned quasi-experimental study of Fu and collaborators (2018) also found respiratory muscle strength improvements in older adults associated with the singing group intervention [10]**.** Another study with a singing therapy intervention showed improvements in pulmonary function, through the reduction of lung hyperinflation, and an increase in arterial blood oxygen saturation. Most participants also reported an increase in exercise capacity and the ability to control symptoms by breathing techniques acquired during the singing lessons, as well as a reduction in anxiety and a perceived improvement in quality of life [36]. Therefore, the learning of breathing techniques and the exercise of breathing control required in singing may be considered an enjoyable lung health promotion activity. Literature reviews on the efficacy of singing programs for lung health, however, found inconsistency in the available results and difficulty in comparing studies due to the diversity of methods and designs [37]. A few studies that evidenced benefits of singing for people with obstructive pulmonary disease showed limited validity due to small sample sizes and no evidence of long-term effects [38]. The findings suggest that the use of singing group therapy may improve older adults’ lung function, as a potential defense against functional decline, however, studies are scarce and more RCT studies are needed to confirm causal and long-term effects.

#### Blood biomarkers

The increase in physical activity and respiratory function stimulated by a weekly singing program may also have an impact on blood biomarkers, such as blood pressure, blood cholesterol, blood glucose, inflammatory and immune biomarkers. For example, Beck et al. (2000) following a naturalistic pre and post-test design during rehearsals and in a public performance found that the mean levels of secretory immunoglobulin A increased significantly - 150% during rehearsals and 240% during the performance. Conversely, cortisol concentrations decreased significantly on average 30% during rehearsals and increased 37% during performance, suggesting that singing activity activates the immune system [39]. Similar results were found by Kreutz et al. (2005), after two rehearsals, where positive affect and secretory immunoglobulin A (S-IgA) increased and negative affect decreased. In another study, saliva samples were collected to assess cortisol and alpha amylase. The results revealed that singing activity had positive influences on affect and social connectedness, however biomarker changes were not significant across all experiments and the unexpected absence of biological effects warrants further investigation [40]. Measuring and analyzing immunity biomarkers, however, is demanding in resources, as proposed by Ryan et al. (2016) and most studies do not follow the right protocol, resulting in lower validity of the results. In this study, due to limited resources, we limited the analysis to inflammatory blood biomarkers [41]. Other biomarkers, such as blood pressure and heart rate, were measured by Valentine and Evans (2001), before and 30 min after a solo singing activity, choir singing and a swimming session among young adults. Engaging in these activities reduced tense arousal and increased energetic arousal, positive hedonic tone and heart rate. The effects were higher in the case of swimming than for singing, with little difference between choir and solo singing [42].

Cardiovascular disease is one of the largest health problems and the leading cause of death among older adults. Intervention and policy approaches are shifting focus to multiple behavior change strategies, targeting problems with common factors. Singing is associated with benefits for health and well-being across the lifespan, with observed changes in the perception of illness, mood, anxiety, and blood pressure levels. However, studies are needed to determine whether such changes are caused specifically by the activity of singing [43]. Very little is known about the effects of enrollment in singing groups on the health biomarkers of participants, such as blood sugar, cholesterol, inflammatory indicators, and blood pressure. In this study, the effects of group singing on a set of health biomarkers are analyzed, expecting to identify wider therapeutic benefits of group singing interventions.

#### Perceived health

From the associations previously reported between participating in group singing and higher well-being and physical and sensory activity, it is possible to hypothesize an impact, not only on the physical health, but also on the perceived health of the participants, such as health-related quality of life (Guralnik et al., 1994) [44], the perception of pain, and related behavioral variables such as the demand for health services and medication intake (Cohen et al., 2006, 2007) [29, 30]. However, some of these results require replication with higher quality methods [9, 31].

#### Perceived benefits of singing

In qualitative studies on the perceptions of older adults’ participation in singing groups, social support and increased interaction between participants, the expression of positive emotions and knowledge acquisition are reported [13], as well as the emotional, physical and mental well-being and learning new things [45]. In this study, interviews will be collected on the perceived motivations, expectations and benefits of those participating in the program, allowing to substantiate the quantitative and qualitative results of the study and thus achieving a higher understanding of the results.

As previously stated, the scientific literature on singing group interventions has demonstrated benefits on the well-being, quality of life, lung function, depression, anxiety, and stress symptoms of older adult participants [28]. However, literature reviews also highlight the lack of RCTs with blinding of conditions and follow-up collection, and limitations of the studies including biased selection of participants, small sample sizes, and selective reporting of outcomes, resulting in the weak validity of some of the results. More RCTs are needed to further validate the benefits of singing groups on the emotional and social well-being, cognitive function and health of the participants (Clark & ​​Harding, 2012; Clift et al., 2016; Dingle et al., 2019) [28, 46, 47].

In this study we aim to overcome some of the gaps in the literature, implementing a pragmatic RCT study, with a 6 months’ follow-up and single-blinded data collection. The protocol of the study was pre-registered to avoid selective outcome reporting. The study enrolls a sample of 140 participants, including young and old older adults from disadvantaged socioeconomic groups, not previously involved in singing groups. This is also a mixed method study with quantitative and qualitative data analysis. The study tests the causal effects of a singing group program on the psycho-emotional, psychosocial, cognitive, and health biomarkers variables, assessed through a series of self-reports, physical trace records, and cognitive and physical performance tests. The study will also qualitatively analyze the participants’ perceptions of their motivations and of the benefits of participating in the program, allowing us to establish relationships with the quantitative results obtained through the RCT design of the study.

Our hypotheses are that participating in group singing will significantly improve the emotional and social well-being, cognitive function, and the general health of the participants after the program, and significantly different to the control group. We also hypothesize that psychoemotional variables (e.g. self-esteem; depression, anxiety and stress), and psychosocial variables (e.g. social identification; loneliness), will mediate the effects of the singing group program on cognitive function (e.g. executive function, verbal memory), well-being and health (e.g. blood biomarkers, respiratory and motor functions) of the participants (see Fig. 1).

**Fig. 1 Fig1:**
[figure not shown]
Biopsychosocial Model of the study depicting the hypotheses of causal effects (Psychosocial, Psychoemotional, Health and Cognitive Outcomes) and mediation effects (Psychosocial, Psychoemotional) of the Singing Program Components (Physical, Cognitive, Social and Emotional)

## Method

### Study design

The present study is a RCT with a crossover design with two conditions (experimental and control), where the participants will be randomly allocated to the two groups. Participants in the experimental group (EG) will take part in the singing group activity, while the control group will be involved in the usual social and artistic activities provided by the social support institution. Data collection will take place prior and after the singing group program and follow-up for the experimental group (6 months after the singing program has finished). The control group will participate in the program after the experimental group and post-test data has been collected from both groups. Semi-structured interviews on the motivations and perceived benefits of participating in the singing group will also be collected on the three times of data collection (see Fig. 2). In this study, we have an immediate intervention group (IG) and waiting-list control group (WLG). After the second assessment (T1), individuals in the control group will crossover to the intervention arm and participate in the singing group program. Thus, this study comprises a randomized experimental phase (T0 to T1 with a within- and a between-groups comparison) and a non-randomized quasi-experimental follow-up phase (T1 to T2 within groups comparison). We opted not to create a specific alternative activity for the control group individuals. Participants are instructed to maintain their daily usual social and leisure activities during the same period. All activities and the duration of the activities developed by the participants during the intervention program and the washout period will be registered for control.

**Fig. 2 Fig2:**
[figure not shown]
Randomized Controlled Trial Crossover design of the study

### Participants

Senior adults, users of the various services of the Santa Casa da Misericordia de Lisboa and Santa Casa da Misericordia de Almada (day-care centers, nursing homes and home care) will be invited by the staff of the institution to participate in an intervention and research program on singing groups. The Santa Casa da Misericordia (SCM) is a Portuguese social support institution whose mission is to improve the quality of life of the less privileged. The inclusion criteria for participants is being 60 years old or older, retired, accepting the invitation to participate in the program, and not having participated in other structured intervention programs in the previous 4 months. Exclusion criteria is having a severe diagnosed impairment that is an impediment for participating in the singing group activity (e.g. severe auditory, visual or mobility impairments). Sample Size. One hundred and forty participants will be invited to participate in the singing program and randomly assigned to an experimental (*n* = 70) or a waiting-list control (*n* = 70) group. A post hoc power analysis shows that this sample will be able to detect a large effect size (n2 = 0.14) with an 88% power. A dropout of 15 participants per group will reduce the study power to 79%. In order to promote adequate enrolment, transport will be provided for participants to attend the intervention sessions. To promote retention and complete follow up, the intervention team and the social support institution promote two social events related to the intervention program. An event for welcoming the second intervention group by the first intervention group will take place, with video presentations and singing together, and a final show with the participation of both intervention groups, after follow-up measurement.

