### Procedures and randomization

The social support institutions’ that are partners of the study will select potential participants, according to the eligibility criteria of the study and their records of the participants. All eligible older adults will be invited to participate in a singing group program, included in a scientific research study. A briefing will be organized by the research and intervention teams to answer the doubts of the potential participants and to explain the content of the informed consent. After the signing of the informed consent, pre-test measures will be collected, and randomization will be performed. The scientific coordinators of the study will set a numerical ordering of the list of participants and, using the SPSS randomization tool, will split up the participants into two equal groups. The social support institution will assign the selected participants to the intervention program. The participants, singing group facilitators and researchers conducting the study cannot be blinded to allocation. However, the collection of the data, namely, cognitive, psychosocial, motor and physiologic outcome measures will be assessed by independent researchers, blinded to group allocation (see Fig. 3).

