### Perceived motivation, expectations and benefits of participating in the program

The study also includes semi-structured interviews on the motivations, expectations and perceived benefits of participating in the program, positive and negative aspects of the program and suggestions for future programs. Also, the control group is asked about in which activities they participated while the first intervention was developing. The same will be asked to the experimental group in the follow up (see Fig. 3). Semi-structured interviews will be performed by researchers after all the other structured questionnaires and tests have been collected. The interviews will be recorded and verbatim transcribed. The content analysis will be performed after reducing the responses to minimal units of meaning, following a categorization by thematic coding according to the objectives of the interviews described above. Two researchers will work on the analysis independently, after which they will meet to discuss the analysis. Any disagreements in the content analysis of the interviews will be resolved through consensus.

All measurements are validated for the study population language with adequate psychometric properties. Additionally, the team will perform psychometric analysis of the measures in the study sample. Assessors will be trained for data collection with guidelines for instruments and measurement procedures, and for working with older adults. Data collection forms can be obtained upon request from the authors. Data entry and coding are subject to two rounds of verification by the peer assessors and by the PI.

Statistical methods include mean comparison of outcome measures (chi-square, t-test, general linear model for repeated measures analysis and ANOVA, after statistical assumptions are verified) between the three times of data collection (pre-test, post-test after 4 months and follow-up after 10 months) and between experimental and control groups. Two experimental sub-groups will be analyzed, as two intervention groups were formed, although with the exact same conditions. Additional, structural equation modelling analysis will be performed to test regression and mediation model hypothesis. No interim analyses are planned. Intention to treat strategies, imputing last observation carried forward, may be used.

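### The stated power (88%, or 79% after dropout) does not follow from the stated effect size and sample size, and no test named in the article reproduces it

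*Protocol article*

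**What the plan says.** The sample-size text stands in the Participants section of the protocol article. It gives the number to be invited ("One hundred and forty participants will be invited to participate in the singing program"), 70 to each arm, and then the power statement: "this sample will be able to detect a large effect size (n2 = 0.14) with an 88% power". The next sentence covers attrition: "A dropout of 15 participants per group will reduce the study power to 79"%. The section on procedures and randomization confirms equal allocation ("will split up the participants into two equal groups").

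The power statement names no alpha, sidedness, test, outcome, correlation between repeated measures, multiplicity adjustment or design effect. The planned group and time comparisons are listed near the end of the Method section as "chi-square, t-test, general linear model for repeated measures analysis and ANOVA, after statistical assumptions are verified", applied "between the three times of data collection" and between arms. Structural equation modelling is added for the regression and mediation hypotheses.

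**The concern.** An eta-squared of 0.14 is a large standardised difference, about 0.8 SD between two equal groups. With 70 per arm an ordinary comparison of means should detect it almost always, so 88% looks too low. The fall to 79% after losing 15 per arm looks too steep, because power near its ceiling changes little with that loss.

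This is the article's only justification of the sample size. If the effect size is wrong, the article misdescribes what the trial can detect. If the powers are wrong, it misdescribes the cost of attrition: losing 15 per arm costs about one point of power at eta-squared 0.14, but about nine points at 0.066. A reader cannot tell which applies.

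**Working it through.** **Inputs.** From the Participants section: eta-squared 0.14; 70 per arm; 15 lost per arm, leaving 55; stated power 88% and 79%. From the randomization section: 1:1 allocation. Assumed because not stated: two-sided alpha 0.05, one comparison, no clustering.

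**Step 1: convert the effect size.**
- f = sqrt(0.14 / 0.86) = 0.403
- d = 2f = 0.807 for two equal groups

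**Step 2: attempt to reproduce the stated power** (noncentral t, noncentrality d × sqrt(n/2), 2n − 2 degrees of freedom).
- n = 70: 0.807 × sqrt(35) = 4.77; critical t 1.977 on 138 df; power 99.7% (stated 88%)
- n = 55: 0.807 × sqrt(27.5) = 4.23; critical t 1.982 on 108 df; power 98.7% (stated 79%)

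The gaps are 99.7 − 88 = 11.7 and 98.7 − 79 = 19.7 points. At this effect size about 31 per arm would already give 88%, and about 25 per arm would give 79%.

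**Step 3: vary the unstated inputs, keeping eta-squared at 0.14.**

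| Set-up | 70 per arm | 55 per arm |
|---|---|---|
| Stated in the article | 88% | 79% |
| Two-sided 0.05 | 99.7% | 98.7% |
| One-sided 0.05 | 99.9% | 99.5% |
| Two-sided 0.01 | 98.4% | 94.4% |
| Two-sided 0.001 | 91.8% | 79.8% |
| Alpha solved to give 88% (about 0.0005) | 88.0% | 73.2% |
| One-way ANOVA, 4 groups, same total sample | 98.6% | 95.1% |
| Repeated measures, 2 or 3 times, correlation 0 to 0.8, lowest value found | 99.2% | 97.0% |

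No row matches both stated figures. The chi-square test in the list compares proportions, and eta-squared does not apply to it.

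**Step 4: back-solve the effect size from each stated power** (two-sided 0.05, eta-squared = d² / (d² + 4)).
- 88% at 70 per arm: d = 0.534, eta-squared 0.0665
- 79% at 55 per arm: d = 0.532, eta-squared 0.0661

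The two powers agree with each other. At eta-squared 0.066 the pair is 87.8% and 78.9%. At the conventional medium value of 0.06 it is 84.3% and 74.7%, so the textbook benchmark does not reproduce it.

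**Step 5: look for set-ups outside the article that fit.**
- Design effect 2.3 with eta-squared 0.14: noncentrality 4.77 / sqrt(2.3) = 3.15 and 4.23 / sqrt(2.3) = 2.79; power 87.8% and 79.0%
- Joint (multivariate) test of 11 outcomes with eta-squared 0.14: 89.9% and 78.3%
- 0.14 entered as Cohen's f in a group-by-time test with three times and correlation 0.3: 87.3% and 77.6%

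The article describes none of these. The third would itself mean that 0.14 is mislabelled as eta-squared.

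**The case against.** The strongest reply is that the powers may be right and only the description incomplete. An article can leave the alpha, test and design effect to a fuller document. Table 1 describes singing in four groups of 30 to 35. With an average of 32.5 and an assumed intraclass correlation of 0.04, the design effect is 1 + 31.5 × 0.04 = 2.26, and power at eta-squared 0.14 is 88.4% and 79.7%, within a point of the stated pair. The match depends on the assumed correlation (0.03 gives 92.5% and 85.2%; 0.05 gives 84.0% and 74.3%) and on group size staying fixed after dropout. The article gives no intraclass correlation and does not say that clustering was allowed for. The reply does not make the sentence reproducible, but it does show that the source of the mismatch is not identified.

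Two stronger readings are tempting. A reader might infer that the 88% and 79% were calculated for a medium effect and that 0.14 is simply a misprint. The back-solved values make this plausible, but Step 5 gives other explanations, one of which keeps 0.14 as it stands. A reader might also infer that the trial is adequate only for very large effects. The article says that a large effect can be detected. It does not say that nothing smaller can.

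It can also be said that the practical harm is limited, and that stands. No allocation, analysis or sample size depends on the correction, and null results can be read from confidence intervals.

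**Conclusion.** The sentence is wrong or incomplete as written. For eta-squared 0.14, a two-group comparison has 99.7% power at 70 per arm and 98.7% at 55, against the stated 88% and 79%. This rests on an assumed two-sided 5% alpha, one comparison, and no clustering or multiplicity correction. No test that the article names, at a conventional alpha, reproduces the stated pair.

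On the same test the stated pair fits eta-squared of about 0.066 (d about 0.53), roughly half the printed value. Whether the effect size, its metric or the powers are at fault, or an allowance went unmentioned, cannot be settled from the document.

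The mismatch is not evidence that the trial is too small. On the simple test the article understates power for the effect it names.

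**What to change.** State in the Participants section the test, outcome, alpha and sidedness, effect-size metric, and any allowance for clustering or multiplicity behind the calculation. Then correct whichever figure is wrong:

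- If it was a simple two-group test aimed at eta-squared 0.14, print 99.7% and 98.7%.
- If it was a simple two-group test and the powers are right, print 88% and 79% for eta-squared of about 0.066 (d about 0.53) and drop the word large.
- If a design effect or joint test was used, say so and give its value (the intraclass correlation and group size, or the number of outcomes).

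The authors should choose among these from their own calculation. The back-solved value should not be adopted as the target merely because it fits. The cost is a sentence or two, with no change to the sample size.
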